### 2.11. Safety

Collection of Adverse Events (AE): only reported AE, either spontaneously by the patient or during interviews with the patient and/or the caregivers during the monitoring of the trial. AE will be collected as soon as the patient signs the Informed Consent up to 30 days after the last visit.

All AE should be documented in the patient’s medical history and in the clinical trial electronic data record.

AE is any adverse health effect in a patient or subject of a clinical trial, although it does not necessarily have a causal relationship to the treatment. An AE may, therefore, be any unfavorable and unintended sign (including an abnormal laboratory finding), symptom, or illness temporarily associated with the use of a research drug, whether or not it is related to the investigational medicinal product.

Adverse Reaction (AR) is any harmful and unintended reaction to a research drug/dispositive, regardless of the dose administered. In the case of an adverse reaction, there is a suspicion of a causal relationship between the investigational drug/dispositive and the adverse event.

Severe Adverse Event (SAE) and Severe Adverse Reaction (SAR) are an adverse event or adverse reaction, which, at any dose:causes the death of the patientthreatens the life of the patientrequires hospitalization or prolongation of patient hospitalizationcauses disability or permanent or major disabilityresults in a congenital anomaly or malformation

All AR will be monitored until their resolution, or at least 15 days after discontinuation of study (whichever occurs first) until the toxicity returns to a grade ≤1, or until the toxicity is considered irreversible.

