### 2.9. Intervention Group

Cases will integrate into their daily routines the designed system (STARR App, DSS, and wearables), measuring at least once a day the vital signs and motor activity during outdoor activities and cycloergometer/pedal exercising. As medical doctors, we will promote a healthy diet, no alcohol or smoking consumption, weight control, blood pressure control, glycemic control, and complications control (e.g., pain, spasticity, falls, infections, etc.).

The designed application will have alarm systems, both for the patient and for the caregiver. The alarms can guide the patient through actions that can recommend to call or go to your primary care physician or go to the emergency services.

The commercial wearable devices will be chosen according to different characteristics: Price, Bluetooth connection, valid for iOS/Android, battery duration, and user’s opinions.

The commercial wearables should be easy to use, comfortable, cheap, and accurate in order to be accessible for the users.

The survivors and the caregivers will be trained about the use of the devices and also about the measures they have to take (e.g., weight, blood pressure, waist circumference) during a period of one week to 10 days.

In case of any technical problem, the user will have a telephone number to put in contact with technical support. If it’s not possible to solve the problem remotely, a technician will go to the participant’s home.

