### 2.10. Outcome Measures

The primary clinical focus in this pilot trial is the evaluation of self-management of the stroke survivors. The proposed primary outcome will be measured by the validated Southampton Stroke Self-Management Questionnaire (SSSMQ) and Family needs of stroke patient questionnaire.

A series of secondary outcomes will be evaluated at different time points, such as the effectiveness of stroke self-management interventions. They rely upon the following items:-Physical function (PF) assessed by the modified BI and Lawton index.-Risk factor reduction (blood pressure, analytical profile -glycemia, HbA1c, lipids, weight, heart rate control, medication compliance).-Self-management behaviors by self-reported information on lifestyles: diet assessed by the Mediterranean diet assessment tool, exercise assessed by tracking with the wearables, smoking, and alcohol consumption.-Healthcare resource utilization by the information available in the public health system in Osakidetza, Cruces university hospital.-Knowledge of condition to assess whether there is a relationship between health literacy and control of cardiovascular risk factors, number of complications, number of recurrences, low adherence to pharmacological and non-pharmacological treatment, and self-management behaviors.-Mood and social isolation by Goldberg scale that measures anxiety and depression.-Stroke Self-management questionnaire (SSMQ).

Other secondary outcomes will be focused on the International Consortium for Health Outcomes Measurement (ICHOM), such as survival, disease control, and acute complications.

All the questionnaires and measurements for the achievement of the outcomes will be collected through face-to-face medical visits in the neuro-rehabilitation department.

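### Section 2.11 collects only reported adverse events while one arm alone is monitored daily, so AE counts by arm are open to unequal detection and unreported admissions can miss the SAE list

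*Protocol article*

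**What the plan says.** All references are to the protocol article.

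- **How AEs are found (section 2.11, Safety).** The rule is "only reported AE, either spontaneously by the patient or during interviews with the patient and/or the caregivers". It makes no distinction by arm.
- **What counts as an AE (section 2.11).** The definition takes in "any unfavorable and unintended sign (including an abnormal laboratory finding), symptom, or illness". Hospitalisation or its prolongation makes an event serious.
- **When (section 2.11).** "AE will be collected as soon as the patient signs the Informed Consent up to 30 days after the last visit".
- **Monitoring in the intervention arm (sections 2.4 and 2.9).** Patients use the system daily, "measuring at least once a day the vital signs and motor activity during outdoor activities and cycloergometer/pedal exercising". Alarms go to patient and caregiver and may advise contacting primary care or going to emergency services. The responsible doctor can manage alarms on a control panel.
- **Monitoring in the control arm (section 2.8).** Standard of care and home recommendations. No device or alarm is described.
- **Common data collection.** Section 2.12 reassesses all patients at months 3 and 6. Table 1 lists stroke recurrences, readmissions, emergency consultations, other consultations and secondary complications at visits (c) and (d), with no split by arm. Section 2.10 adds survival, acute complications and "Healthcare resource utilization by the information available in the public health system in Osakidetza, Cruces university hospital".
- **Use of the safety data.** Section 2.2 lists adverse events that the system may cause among the matters to be evaluated. Section 2.14 gives a general rule for comparing groups and does not name AEs. Section 2.4 states that the trial is open.

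**The concern.** A rule that relies on reporting yields what patients and caregivers have noticed. In this trial the intervention shows one arm's patients and caregivers more: daily readings, and alarms sent to the same people whose reports define an AE. With a definition that reaches down to single signs, the same wording can produce different counts in the two arms when true risk is the same. No step in the article equalises detection.

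At stake is the reading of the stated safety objective. An excess of AEs under STARR could be harm or closer observation, and a real reduction could be hidden by better detection. Counts alone would not tell these apart.

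A second, separate weakness lies in the word *only*. An admission found in the utilisation data but mentioned by nobody is an SAE by the protocol's own definition, yet falls outside its collection rule. This can happen in either arm. It is incompleteness rather than detection bias, and it could leave the SAE list and the utilisation table in disagreement.

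**Working it through.** The article gives no AE rate, detection rate or safety power, so there is no figure to reproduce. The check sets the passages side by side and then shows by simple arithmetic what unequal detection would do.

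**1. Is the chance of detection the same in both arms?**

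| Route by which an event can become known | Intervention | Control |
|---|---|---|
| Spontaneous report (2.11) | yes | yes |
| Interview with patient or caregiver (2.11) | yes | yes |
| Visits at months 3 and 6 (2.12, Table 1) | yes | yes |
| Laboratory tests at visits (Table 1) | yes | yes |
| Vital signs at home at least daily (2.9) | yes | not described |
| Alarms to patient and caregiver (2.9) | yes | not described |
| Doctor's alarm panel (2.4) | yes | not described |

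The first four rows are common to both arms and the last three are not. The gap concerns signs and alarm-prompted contacts rather than laboratory findings, which are scheduled alike. Section 2.8 describes control visits every six months in the first year, while section 2.12 has all patients seen at months 3 and 6. These two sections must be reconciled, because the number of contacts in controls bears on this table.

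**2. What would unequal detection do?** Let π be the true proportion of patients with an AE, and d the probability that it is reported. Then

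observed proportion = π × d, and with equal π the apparent risk ratio = d(intervention) / d(control), and the apparent risk difference = π × [d(intervention) − d(control)].

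All values of π and d below are assumptions.

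| d, intervention / control | Apparent risk ratio | Difference at π = 20% | π = 40% | π = 60% |
|---|---|---|---|---|
| 80% / 80% | 1.00 | 0 points | 0 points | 0 points |
| 90% / 70% | 0.9/0.7 = 1.29 | 4 points | 8 points | 12 points |
| 90% / 50% | 0.9/0.5 = 1.80 | 8 points | 16 points | 24 points |

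The reverse also holds. With detection at 90% and 70%, a true risk ratio of 0.7/0.9 = 0.78 would appear as 1.00.

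**3. Can a serious event be missed?** Suppose a patient is admitted and neither patient nor caregiver mentions it. Under section 2.11 it is not collected as an AE. Under section 2.10 it can appear in the health-system records. Up to visit (d) the Table 1 readmission item may also catch it. In the 30 days after visit (d) no Table 1 column remains, so of the sources shown only a spontaneous report or the records could find it.

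**The case against.** The strongest reply has three parts.

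*No between-arm AE test is stated.* Section 2.2 lists adverse events beside accessibility, sustainability and satisfaction, which reads as evaluation of the system. This stands as far as it goes: the comparison follows only from that objective and the general rule in section 2.14. But in a randomised trial the control arm is the natural reference for what the system causes, and AE counts will be read by arm.

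*Serious events are already collected in both arms.* This stands, and it narrows the point. Table 1 and section 2.10 cover readmissions, recurrences, complications and survival without a split by arm. What is missing is a link from those data to the AE and SAE list.

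*Some asymmetry is inherent when the intervention is itself monitoring.* This is also true, and no fix removes it. Alarms can prompt emergency visits, and patients who have seen alarms may say more at interview.

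Several stronger readings are tempting but not supported:

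- A reader might infer that the comparison *is* biased. The documents support only a risk of bias. More reported events under STARR is the plausible direction, but neither size nor direction can be fixed from them.
- A reader might count measurement days. About 182 days against 2 visits, with an assumed independent 1% chance of an abnormal reading each time, gives 1 − 0.99^182 = 84% against 1 − 0.99^2 = 2%. That is the chance of at least one abnormal reading, not an AE rate. Section 2.11 does not turn a reading into an AE, one person's readings are correlated, and the 1% is not in the documents.
- A reader might infer that controls are questioned only at two visits, or that glucose is measured daily. Section 2.11 does not confine interviews to visits. Section 2.9 speaks of vital signs and motor activity; a glucometer is listed in section 2.4 without a daily schedule.

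**Conclusion.** The point holds as a risk, not as demonstrated bias. Three things are stated in the article: AE collection is restricted to reported events, daily measurement and alarms exist in one arm only, and the trial is open. No measure to equalise detection is described. It follows that AE counts by arm may partly reflect surveillance. The apparent risk ratios of 1.29 and 1.80 rest wholly on assumed detection probabilities and equal true risk. They show that moderate differences in reporting could matter; they do not predict the result.

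The incompleteness of the SAE list follows directly from the word *only* and the protocol's own definition of a serious event, without any assumption about detection rates. How often it would occur cannot be known from the article. Together these justify a modest change to section 2.11. They do not call the trial's efficacy comparison into question.

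**What to change.** In section 2.11:

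1. Delete *only* before the reference to reported AEs.
2. For every randomised patient, add to the AE/SAE list the deaths, admissions and recurrent strokes found in the Table 1 items or the Osakidetza records, through the stated window to 30 days after the last visit.
3. Base any between-arm safety comparison on these events and on an identical AE interview at visits (c) and (d).
4. Report emergency visits by arm, marking those prompted by an alarm, since the intervention can itself generate them.
5. List signs known only from STARR devices or alarms separately for the intervention arm, outside the comparison.

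Sections 2.8 and 2.12 should also be reconciled on visit frequency.

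The cost is protocol wording and one further extraction from records the trial already plans to use. There are two small downsides. Deciding which events are device-only or alarm-prompted takes some judgement in an open trial, so the rule should be written down beforehand. Device-only signs also leave the comparative table, though they remain reported. Deaths, admissions and recurrent strokes are less exposed to unequal detection but not immune, because an alarm may lead to an admission; the report should say so.

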## Abstract

Background: Stroke is a leading cause of severe and long-term disability in developed countries. Around 15 million people suffer a stroke each year, being most of them ischemic due to modifiable risk factors. Adequate self-management abilities may help to manage the consequences of stroke, but it is unknown which specific intervention could be effective to booster these self-management abilities. Objective: To evaluate the improvement of self-management in chronic stroke survivors using decision support and self-management system (STARR). Methods: A randomized, prospective, parallel group, open, and the unicentric pilot trial will be performed. Stroke survivors and their caregivers will be randomly allocated to STARR management or standard of care. Main inclusion criteria are mild to moderate disabled first stroke adult survivor, living at home, able to cope and follow the guidelines and devices, without socio-familial exclusion. All will get a conventional treatment in the acute and subacute phase; however, in the chronic period, cases will use the developed STARR App and Decision Support System. Measurements will be performed at baseline, at 3 months, and at 6 months. Outcome measures are patient-report outcome measure of self-management competency, physical function, risk factor reduction, healthcare resource utilization, knowledge of the condition, mood, and social isolation. Discussion: If effective, the results of this study will enable stroke patients and their caregivers to deal better with the everyday life obstacles of stroke, improve the adherence of the treatment, improve the control of cardiovascular risk, and, in consequence, reduce the recurrence of secondary strokes, the number of complications, the number of consultations, and readmissions; to ultimately reduce the health systems costs. Taking into consideration that the number of stroke survivors is increasing around the world, a large number of individuals could profit from this intervention.

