### 2.2. Secondary Objectives

Improvement of the study participants’:Self-management.Level of independence in the activities of daily living (ADL).Quality of life.Adherence to home-based rehabilitation and pharmacological and non-pharmacological treatment.Need for caregivers (family, care providers…).Recurrent stroke and the complications related to stroke.A number of hospital readmissions, emergency care, and outpatient visits to the hospital and primary care centers.

Also, the study will evaluate:Cost-effectiveness of the developed system.Accessibility of the developed system.Sustainability of the developed system.User’s satisfaction (by users, we mean stroke survivors, caregivers, and professionals using the developed system).Possible adverse events that the system can cause on the study participants.

In addition, the efforts will be made to identify new variables related to the prognosis of stroke.

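### Section 2.11 ties adverse-event collection to the patient and gives no workable route for a caregiver's own event, although caregivers are randomised and use the system

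*Protocol article*

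**What the plan says.** **The safety rules (Protocol article, 2.11).** The source of reports is "only reported AE, either spontaneously by the patient or during interviews with the patient and/or the caregivers during the monitoring of the trial". The window is "AE will be collected as soon as the patient signs the Informed Consent up to 30 days after the last visit". The filing rule is "All AE should be documented in the patient’s medical history and in the clinical trial electronic data record". The seriousness criteria on death, threat to life and prolonged hospitalisation name the patient. The definition is wider: "AE is any adverse health effect in a patient or subject of a clinical trial".

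**The harms objective (2.2).** The study will evaluate "Possible adverse events that the system can cause on the study participants".

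**The caregivers' place in the trial.** The Abstract says "Stroke survivors and their caregivers will be randomly allocated to STARR management or standard of care". Section 2.5 lets caregivers as well as survivors revoke consent, and 2.6 recruits caregivers together with the survivors. Section 2.9 trains both on the devices and adds "The designed application will have alarm systems, both for the patient and for the caregiver". Section 2.10 makes the family needs questionnaire part of the primary outcome, and Table 2 schedules it for caregivers. Table 2 also gives caregivers the System Usability Scale, the SF-36 and the Caregiver Strain Index.

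**The concern.** Caregivers are not bystanders here. They are allocated, consent, handle the devices, receive alarms and supply part of the primary outcome, and the Discussion looks for a better quality of life for them as well as for the survivors. A trial that seeks benefit in a group should be able to see harm in the same group.

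Section 2.11 does not clearly allow that. A caregiver harmed in connection with the system, for example through anxiety provoked by alarms, has no start date for collection, no spontaneous reporting route and no medical file of their own. Section 2.5 even foresees a severe illness of the principal caregiver as a reason for withdrawal, but 2.11 does not say whether that illness is also an adverse event. At stake is how far a safety statement about the system can reach: without a stated rule, an absence of caregiver events in the report could mean that none occurred or that none was sought.

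**Working it through.** No statistical figure is involved, so the check is a comparison of the rules in 2.11 with the caregivers' role.

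**Step 1. Each operative rule, and whom it names.**

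| Element of 2.11 | Tied to | Caregiver's position |
|---|---|---|
| Start of collection | the patient's consent | no start point of their own |
| Spontaneous report | the patient | not mentioned |
| Interview | patient and/or caregivers | interviewed; not said about whose events |
| Filing | the patient's medical history, plus the trial electronic data record | only the second could fit |
| Seriousness: death, threat to life, prolonged hospitalisation | the patient | not mentioned |
| Definition of an adverse event | a patient or a trial subject | can be read to include them |

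The sentence on sources names the patient and the caregivers as different people. Within 2.11, therefore, the word patient is most naturally the survivor.

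**Step 2. Try both readings.**
- *Narrow* (events of survivors only): a randomised and exposed group has no event collection.
- *Wide* (the definition's trial subject includes caregivers): the filing rule applies to all events, so a caregiver's health event goes into the survivor's medical history, and the caregiver's window opens when somebody else signs.

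Neither reading gives a workable route.

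**Step 3. Whom the harms objective covers.** In 2.2 the term *study participants* heads a list of survivor outcomes (daily living, need for caregivers, recurrent stroke). Caregivers come in through another term, *users*, which is expressly defined to include them. This favours the narrow meaning. On the other side, 2.6 recruits survivors together with their caregivers and then describes all participants as volunteers who have signed consent, and 2.5 shows that caregivers consent. The term is ambiguous.

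**Step 4. Whether scheduled scales fill the gap.** Table 2 gives caregivers the Caregiver Strain Index and SF-36 at baseline and final visit (SF-36 also at the event visit), and neither at the first follow-up visit. They yield scores. They do not record an individual event, its date, its seriousness or its relation to the system.

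**Step 5. Size.** The documents give no caregiver count; 2.13 counts survivors. Assuming one caregiver per survivor and the 1:1 ratio of 2.6:
- with the 40 patients of 2.4: 40 / 2 = 20 caregivers in the STARR arm;
- with the 80 patients of 2.13: 80 / 2 = 40.

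The caregivers' share of all enrolled people is r / (1 + r), where r is the number of caregivers per survivor. At r = 0.5, 0.8, 1 and 1.2 this is 33%, 44%, 50% and 55%.

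**The case against.** The strongest reply is that no sentence limits collection to patients. The definition reaches any trial subject, caregivers are interviewed, and every event also goes into the trial electronic data record, so a caregiver's event could be recorded there. Section 2.5 uses the word patients loosely enough to cover caregivers. If *study participants* in 2.2 means survivors, the objective and 2.11 agree. Caregiver burden is measured by two scales. And an article that condenses a fuller protocol may leave forms and codes to that document.

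Much of this stands against a stronger reading. A reader might infer that adverse events are collected and filed for patients only, and that half of the randomised people are outside safety surveillance. The documents do not say the first, for the reasons just given. The second needs a caregiver count that they do not contain.

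It does not remove the narrower point. The loose usage in 2.5 does not carry over, because 2.11 itself separates the patient from the caregivers. The definition is generic (it goes on to speak of a research drug), and applying it to caregivers leads to the misfiling shown above. Nor is this a detail left to a fuller document: the article states the start point, the reporter and the filing place, and each is worded for the patient.

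**Conclusion.** The concern holds in a limited form. Section 2.11 gives no workable route for a caregiver's own adverse event, and 2.2 leaves open whether the harms objective includes caregivers. This rests on the wording alone and on no statistical assumption.

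It should not be put as a direct contradiction between objective and safety section, because *study participants* may mean survivors. Nor can a share of people missed or a number of lost events be claimed as fact. The figure of about 20 or 40 STARR caregivers assumes one per survivor and depends on which of the two patient numbers applies, and the documents give no basis for a caregiver event rate. The consequence is modest: it limits what can be said about caregiver safety and does not touch the efficacy comparison. The correction is cheap enough to make.

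**What to change.** In 2.11:
- state that adverse events are collected for survivors and caregivers in both arms, each from their own consent until 30 days after the last visit;
- ask caregivers about their own events at the month 3 and month 6 assessments, and accept their spontaneous reports;
- record caregiver events under the caregiver's own code in the trial electronic data record, not in the patient's medical history;
- word the seriousness criteria for the affected person;
- tabulate caregiver events separately, by arm.

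In 2.2, define *study participants* and say whether caregivers are included in the harms objective.

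The cost is some protocol wording, one question at assessments that Table 2 already schedules for caregivers, and a caregiver code (2.15 describes codes for patients only). The downside is a few extra event forms and one more safety table.

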### 2.12. Follow-up Period

All patients recruited for the research clinical trial (RCT) will be reassessed during external consultations at month 3 ± 1 week (1^st^ visit) and at month 6 ± 1 week (final visit).

All the participants will get the same reassessment at the event day (evaluation a), recruitment visit (evaluation b), 3 months later (evaluation c), and 6 months of follow-up (evaluation d) taking into consideration that not all the tools are administered at each time.

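### Section 2.11 gives the follow-up of adverse reactions a limit that is both a minimum and a stopping point, so when follow-up ends cannot be determined

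*Protocol article*

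**What the plan says.** Three statements in the protocol article bear on this.

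- **Follow-up of adverse reactions (section 2.11).** "All AR will be monitored until their resolution, or at least 15 days after discontinuation of study (whichever occurs first"). The sentence does not stop there. It continues, with no linking word, "until the toxicity returns to a grade ≤1, or until the toxicity is considered irreversible".
- **Collection of adverse events (section 2.11).** "AE will be collected as soon as the patient signs the Informed Consent up to 30 days after the last visit".
- **Objectives (section 2.2).** Among the things the study will evaluate is "Possible adverse events that the system can cause on the study participants".

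The follow-up rule counts from discontinuation of the study. The collection rule counts from the last visit. The article does not say how the two dates relate.

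**The concern.** The 15-day limit is worded as a floor, and the parenthesis then makes it one of two events of which the earlier ends follow-up. Site staff cannot obey both. One person could close an unresolved reaction on day 15 and another could follow the same reaction until it settles, and each could point to the text.

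Harm caused by the system is a stated subject of evaluation, and section 2.11 counts lasting or major disability among its seriousness criteria. Whether a reaction meets that criterion may not be clear by day 15. A rule that permits closure on that day works against the objective, and it also leaves the patient without a required safety check while the reaction is still open.

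**Working it through.** The plan gives no statistical figure to reproduce here. The check is a reading of the sentence and a subtraction of two time windows.

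**Step 1: the parts of the follow-up sentence.**

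| Part | Wording | Effect |
|---|---|---|
| a | "All AR will be monitored until their resolution" | ends at resolution |
| b | "at least 15 days after discontinuation of study (whichever occurs first") | a minimum of 15 days, and also a stop on day 15 if that comes before resolution |
| c | "until the toxicity returns to a grade ≤1, or until the toxicity is considered irreversible" | ends at grade 1 or below, or at irreversibility |

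**Step 2: does any reading give every part a function?**

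- If the parenthesis governs, follow-up ends at resolution or on day 15, whichever is earlier. The minimum is then no minimum, and part c does nothing for a reaction still open on day 15.
- If the minimum governs, follow-up runs for 15 days or longer, and the parenthesis has no effect.
- If part c governs, follow-up runs to grade 1 or below or to irreversibility, and the parenthesis again has no effect.

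No reading uses all the words. The sentence is inconsistent whatever its authors intended.

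**Step 3: comparison with the collection window.** Section 2.11 describes an adverse reaction as a case where "there is a suspicion of a causal relationship between the investigational drug/dispositive and the adverse event". Reactions are therefore a subset of adverse events and fall inside the collection window, which runs to day 30 after the last visit. The last scheduled visit is "at month 6 ± 1 week (final visit").

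Let *k* be the number of days by which discontinuation follows the last visit (negative if it comes earlier). The article does not give *k*, so it is varied here.

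- **The parenthesis governs.** Required follow-up ends on day 15 + *k* after the last visit. The part of the window beyond it is max(0, 30 − (15 + *k*)) = max(0, 15 − *k*) days.
  - *k* = 0 (same day): 15 days, that is, onsets on days 16 to 30.
  - *k* = 15 or more: 0 days.
  - *k* = −10 (for example, withdrawal ten days before a last visit taken as the scheduled one): 25 days.
- **The minimum or part c governs.** Day 15 is not a stop, and the gap is 0 days.

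The sign of *k* is open because section 2.5 allows withdrawal at any time, and the article does not say whether the last visit means the last one scheduled or the last one attended.

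**The case against.** The best defence is that the intent can be guessed: follow each reaction until it resolves, reaches grade 1 or below or proves irreversible, with 15 days as the minimum. The final clause of the sentence supports that, and on that reading nothing is lost. The defence also notes that collecting events and following reactions are different tasks and may have different time limits, that section 2.11 requires every adverse event to be documented in the medical history and the electronic trial record, and that a reaction during the six-month intervention would usually have had long observation before day 15 after the end became relevant.

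Most of this stands, and it limits what may be concluded. Four stronger inferences are tempting, and the documents do not support them.

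- **That late reactions certainly get no follow-up.** This needs the parenthesis to override the rest of the sentence, and it needs the two anchor dates to coincide. The article establishes neither.
- **That the 30-day and 15-day periods contradict each other.** They govern different tasks. They are mismatched under one reading only.
- **That half of the post-study period is lost, or that lasting harm will be under-counted.** Fifteen days out of 30 is a share of calendar time and not of events. The article gives no reaction rate or timing, and nothing in it forbids recording a later outcome.
- **That the lack of a named grading scale is a defect.** A condensed article may leave the scale to the full protocol.

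What the defence does not remove is the need to guess. The article states a safety rule, and its words permit the closure that the presumed intent would forbid.

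**Conclusion.** The follow-up rule for adverse reactions is wrong as written. Its minimum, its parenthesis and its final end points cannot all apply, and a literal reading lets follow-up of an unresolved reaction stop 15 days after discontinuation. This conclusion rests on the wording of one sentence and on no assumption.

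The mismatch with the collection window is conditional. It amounts to 15 days (onsets on days 16 to 30) if the parenthesis governs and discontinuation is the day of the last visit. It shrinks to nothing if discontinuation comes 15 or more days later or if another part of the sentence governs, and it exceeds 15 days if discontinuation comes earlier. The number of patients affected cannot be estimated from the document, and only reactions still open at the end of study or starting after it are concerned.

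This is a defect in a safety rule. It does not touch randomisation, the primary outcome or the primary analysis. It should be corrected because the correction is cheap and it protects patients.

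**What to change.** Delete the parenthesis in section 2.11 and rewrite the sentence along these lines: each adverse reaction is followed until it resolves, returns to grade 1 or below, or is judged irreversible; any reaction still open is followed at least to day 30 after the last visit, and day 30 is a minimum and not a stop.

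Use the last visit as the anchor for both collection and follow-up, and say which visit that is for a patient who withdraws early.

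The cost is one or two sentences, submitted to the Ethics Committee as section 2.15 requires for any modification, and a few extra telephone calls or record checks for patients with an open reaction. No visit, sample size or analysis changes.
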